##### Outcome measures

*Psychological measures*
Children’s Depression Inventory (CDI 2 [44];), which measures self-reported depressive symptoms in youth aged 7–17 years and takes 5–15 min to complete (primary outcome for the potential full trial)Positive and Negative Affect Schedule (PANAS [65];), with two 10-item sub-scales for positive and negative affectNew General Self-Efficacy scale [66], an eight-item measure to assess how much people believe they can achieve their goals to engage in exerciseMultidimensional scale of perceived Social Support (MSPSS [67];), a twelve-item measure designed to measure perceptions of support from family, friends, and a significant otherA six-item COM-B measure asking participants how much they agree that they have the Capability (Physical and Psychological), Opportunity (Social and Physical), and Motivation (Reflective and Automatic) to be regularly active [68].

##### Carer measures

Burden Scale for Family Caregivers – short form (BSFC-s [69];) is a ten-item scale to measure perceived burden on families.

##### Physical activity

Peak and average heart rate (Polar, H10, Polar Electro, Kempele, Finland) and rating of perceived exertion during the intervention sessions [70]. Physical activity beyond the intervention sessions by accelerometer (GENEActiv Original, Activinsights, Cambridgeshire, UK) and the Youth Physical Activity Questionnaire (Y-PAQ [71];).

##### Trial intervention safety

For trial intervention safety, adverse events are recorded.

##### Economic evaluation

EQ-5D-5L, a measure of Health-Related Quality of Life (HRQoL [72];) uses both descriptive scales (five items) and a visual scale (EuroQol Visual Analogue System (EQ-VAS)); Child Health Utility 9D (CHU-9D [73];). A HRQoL questionnaire which will take approximately 5 min to complete. There are nine multiple-choice questions, each with a choice of five answers; modified client service receipt inventory (CSRI [74];) completed with the MHSW. If the young person is unable to complete this measure, then the parent/carer will be asked to provide missing information.

##### Process evaluation

A process evaluation will be conducted to identify and address key issues to inform and facilitate the main trial. It will examine intervention delivery and contamination between arms, barriers and facilitators to engagement of young people, and recruitment methods. The findings will be used to refine the intervention and study delivery for the main trial. Mixed methods used will include:
Intervention logs completed by the REPs and MHSWs to examine intervention delivery and adherence, including numbers of young people attending, activities undertaken, and duration of each activity.Independent observations of 5–10% of the intervention sessions using an observation checklist to ascertain fidelity to the training.Focus groups with young people after the intervention sessions are completed (one focus group per site). Purposive sampling will be used to invite a diverse mix of young people to the focus groups. A semi-structured topic guide will be used to explore acceptability of the intervention and study methods, and barriers and facilitators to participation.Focus groups with the REPs and MHSWs involved in intervention delivery, in order to explore experiences of training and delivery (one focus group per site). A semi-structured topic guide will be used to explore experiences of intervention training and delivery.Case report forms will record young people’s reasons for declining to participate in order to inform recruitment strategies in the main trial. We will also record non-identifiable demographic information such as ethnicity and sex.

#### Data management

The database will assign participants a unique study participant identifier (PID) and all data will be entered against this number. The central database will be controlled and administered by NCTU Data Management. Features to help maintain data quality include the following: maintaining an audit trail; allowing users to raise data query requests; search facilities to identify validation failure/missing data.

#### Statistical methods

Data analysis for the feasibility study will be largely descriptive. The referral, recruitment (> 10% of potential young people recruited), and retention (> 66% attendance at intervention sessions) will be evaluated, reporting the proportions (and confidence intervals) of young people reaching each stage of the study, by referral source and study arm. Reach and representativeness will be described in relation to the proportions of young people who are screened for participation and are randomised, and in comparison, to the characteristics of local populations. Adherence will be assessed through the proportions of sessions attended and the average heart rate achieved compared to the target for the intervention. Behaviour change, in terms of increased physical activity beyond the intervention sessions, will be measured by accelerometer and self-report data at 14 and 26 weeks. Feasibility of collecting outcome and resource use data will be evaluated by estimating the proportions of missing data in each of the outcomes assessed. The outcome measures will be summarised, by study arm, using descriptive statistics based on the intention-to-treat principle. No formal comparison of the groups will be made. To monitor safety, the number of adverse events will be reported by study arm. 

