##### High-intensity exercise arm

This is composed of high-intensity exercises of alternating training sessions [45, 46] (e.g. basketball, football, boxing drills—see Table 1 for full breakdown) beginning with a 10-min warm up, culminating with a 5-min whole body cool down. Young people will perform four repetitions of 45 s of maximal effort exercise (> 90% predicted maximal heart rate) with 90 s rest in between each repetition (approximately 9 min). This will increase by 2 min and 15 s every 2 weeks (e.g. one repetition of 45 s of exercise and 90 s rest) for the first 6 weeks and 4 min 30 s (e.g. two repetitions of 45 s of exercise and 90 s rest) in the last 6 weeks. The final 2 weeks will be 12 repetitions (27 min of exercise). Heart rate monitors will be used to tailor each person’s maximum intensity and measure exertion in each session [47].

**Table 1 Tab1:** Exercise session outline

Week	Session number	High-intensity exercise component	Low-intensity exercise component
1	1	10 min warm up Boxing (4 reps of 45 s and 90 s rest) 5 min cool down **Total time: 24 min**	10 min warm up Walking football (7.5 min halves) *2 min rest at half time* 5 min cool down **Total time: 32 min**
	2	10 min warm up Circuit training to music (4 reps of 45 s and 90 s rest) 5 min cool down **Total time: 24 min**	10 min warm up Walking netball (7.5 min halves) *2 min rest at half time* 5 min cool down **Total time: 32 min**
2	3	10 min warm up Football (4 reps of 45 s and 90 s rest) 5 min cool down **Total time: 24 min**	10 min warm up Walking basketball (7.5 min halves) *2 min rest at half time* 5 min cool down **Total time: 32 min**
	4	10 min warm up Basketball (4 reps of 45 s and 90 s rest) 5 min cool down **Total time: 24 min**	10 min warm up Walking dodgeball (7.5 min halves) *2 min rest at half time* 5 min cool down **Total time: 32 min**
3	5	10 min warm up Choice/combination (5 reps of 45 s and 90 s rest) 5 min cool down **Total time: 26 min 15 s**	10 min warm up Walking choice (9 min halves) *2 min rest at half time* 5 min cool down **Total time: 35 min**
	6	10 min warm up Boxing (5 reps of 45 s and 90 s rest) 5 min cool down **Total time: 26 min 15 s**	10 min warm up Walking choice (9 min halves) *2 min rest at half time* 5 min cool down **Total time: 35 min**

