### Process evaluation

Triangulation of the analysis of the intervention logs, focus groups, and case report forms will be used to describe and examine adherence and delivery of all three arms in order to refine the intervention for the full-scale trial. Intervention logs will be rated against the adherence checklist by members of the study team, to identify implementation fidelity and any potential contamination between arms. The focus groups will be transcribed verbatim and thematically analysed [75] using NVivo software. The findings from the focus groups with REPs and MHSWs will be synthesised with the intervention logs and independent observations of the sessions to explore adherence to training content and importantly to offer explanations for adherence and non-adherence. The findings from the focus groups with the young people will be considered along with the fidelity information from intervention logs and observations and quantitative adherence data (i.e. proportions of sessions attended and average heart rate). This will identify necessary modifications to the intervention for the main trial and to generate hypothetical propositions of the circumstances of successful delivery in the main trial.

We will examine reasons for declining to participate in the study and any demographic patterns amongst decliners to facilitate reach and representativeness of our recruitment strategy in the main trial. With reference to particular groups and local strategies outlined by Active Partnerships, recruitment strategies will be reviewed to aid our interpretation of recruitment figures for hard to reach groups of young people, which will then inform any recommended changes to recruitment strategy in the full-scale trial. This analysis will enable us to identify contextual factors that may affect adoption, delivery, and maintenance of the intervention.

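### The adherence analysis compares average heart rate with a high-intensity target that applies only to the 45 s work bouts, so it would probably understate adherence in that arm

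*Protocol article*

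**What the plan says.** All references are to the protocol article.

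- **Adherence metric.** Statistical methods: "Adherence will be assessed through the proportions of sessions attended and the average heart rate achieved compared to the target for the intervention". The Process evaluation section after it describes the same quantity as "quantitative adherence data (i.e. proportions of sessions attended and average heart rate"). Both name the average only.
- **High-intensity target.** The High-intensity exercise arm section starts from "four repetitions of 45 s of maximal effort exercise (> 90% predicted maximal heart rate) with 90 s rest in between each repetition (approximately 9" (the last figure is in minutes). The 90% figure is attached to the work repetitions. No heart-rate target is given for the rests, the warm-up, the cool-down or the session as a whole.
- **Rest of the session.** The same section has it "beginning with a 10-min warm up, culminating with a 5-min whole body cool down". At the top of the progression, "The final 2 weeks will be 12 repetitions (27 min of exercise").
- **What is collected.** Physical activity, under Outcome measures: "Peak and average heart rate (Polar, H10, Polar Electro, Kempele, Finland) and rating of perceived exertion during the intervention sessions". The study schedule (Table 3) also lists both peak and average heart rate. The period over which the average is taken is not defined.
- **Use of the result.** The abstract lists adherence to, and ability to reach, intensity among the outcomes. Under Feasibility outcomes, the traffic-light system covers adherence. Its named criteria are attendance above 66% and questionnaire completion above 80%, and the wording leaves room for others. No heart-rate threshold is stated.

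**The concern.** The metric and the target refer to different periods. The target describes the short maximal efforts. The average, on its natural reading, also includes recovery, which is meant to be easier. A participant can do exactly what is prescribed and still show an average well under 90%.

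The distortion is not shared equally. The low-intensity arm is almost continuous activity judged against a 40% to 50% band, so its average is much closer to the quantity that its target describes. Exercise intensity is the contrast that the energy matching is meant to isolate. A low adherence figure produced by the metric could be read as young people with depression being unable to reach high intensity, and could prompt changes to the intervention that the data do not support.

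**Working it through.** All heart rates are percentages of predicted maximum.

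**Inputs from the article.** Bout 45 s, rest 90 s, warm-up 10 min, cool-down 5 min, 4 repetitions in weeks 1-2, 12 repetitions in weeks 11-12, bout target above 90%.

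**Step 1: reproduce the article's durations.** Block = repetitions × (45 + 90) s; session = 10 min + block + 5 min.
- 4 repetitions: 4 × 135 s = 9 min; session 24 min.
- 12 repetitions: 12 × 135 s = 27 min; session 42 min.

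Both match the text and Table 1, as do the 5, 6, 8 and 10 repetition stages (26.25, 28.5, 33 and 37.5 min).

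**Step 2: share of time to which the target applies.**
- Of the block: 45/135 = 33.3%. If the last rest is not counted: 180/450 = 40% with 4 repetitions and 540/1530 = 35.3% with 12.
- Of the session: 3/24 = 12.5% in weeks 1-2; 9/42 = 21.4% in weeks 11-12.
- For comparison, the low-intensity block in week 1 is two 7.5 min halves with a 2 min rest, so 15/17 = 88% of it is activity.

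**Step 3: break-even, with no assumption about recovery.** With bouts at w and rests at r, block average = w/3 + 2r/3. Setting this to 90 gives r = (90 − w/3) × 3/2.
- w = 90: r = 90.
- w = 95: r = 87.5.
- w = 100: r = 85. If the last rest is dropped with 4 repetitions, (90 − 0.4 × 100)/0.6 = 83.3, the lowest value.

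For a whole-session average of 90 with bouts at 100, everything outside the bouts must average:
- Week 1: (90 − 0.125 × 100)/0.875 = 88.6.
- Week 12: (90 − 0.214 × 100)/0.786 = 87.3.

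**Step 4: likely size, under stated assumptions.** The article gives no recovery, warm-up or cool-down heart rates. Assume bouts at 95, rests at 60 to 85, and warm-up and cool-down at 60 to 70.
- Block average: 95/3 + 2 × 60/3 = 71.7, up to 95/3 + 2 × 85/3 = 88.3.
- Whole session, week 1: (71.7 × 9 + 60 × 15)/24 = 64.4, up to (88.3 × 9 + 70 × 15)/24 = 76.9.
- Whole session, week 12: (71.7 × 27 + 60 × 15)/42 = 67.5, up to (88.3 × 27 + 70 × 15)/42 = 81.8.

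All are below 90, although every bout met the target.

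**Step 5: drift.** With bouts at 95, rests at 70, and warm-up and cool-down at 60, the block average is 78.3. The session average is then 66.9 in week 1 and 71.8 in week 12. It rises by about 5 points with no change in effort, because the block becomes a larger part of the session.

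**The case against.** The strongest reply is that the article never says session average. It gives no averaging window, and recording heart rate during a session says when it is collected, not how it is summarised. An average over the work bouts alone is not excluded, and a condensed article may leave the window to a fuller document. This stands in part: the session or block reading is an inference. But nothing in the article points to a bout-only average, and the Physical activity section ties both peak and average to the sessions. Both adherence statements also name the average and leave out the peak, the collected variable closer to the target.

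A reader might go further and infer that fully adherent participants will be scored as failing, or that the high-intensity arm is bound to look non-adherent and so trigger a stop. The article does not support this. It states no heart-rate cut-off, no classification of participants and no heart-rate progression criterion, and it calls the analysis largely descriptive. Adherence is also judged from attendance, intervention logs, observations and focus groups. Peak heart rate and perceived exertion are collected and may well be reported beside the average.

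Nor is it impossible to average 90%: Step 3 gives the conditions. The size of the shortfall depends on assumed recovery rates, and over the interval block it could be under 2 points (90 − 88.3 = 1.7).

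**Conclusion.** The point holds as a mismatch between metric and target. If average heart rate is taken over the interval block or the session, the planned comparison would very probably understate adherence in the high-intensity arm, and more so than in the near-continuous low-intensity arm. The break-even figures rest only on the article's own timings: rests must average at least 85% for the block to average 90%, even with bouts at 100% (83.3% if the last rest is dropped in the shortest session). The expected block average of about 72% to 88% rests on assumed recovery rates.

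The consequence is a biased descriptive result on a listed feasibility outcome. It feeds the traffic-light judgement and the choice of modifications for the main trial, but does not decide either by itself.

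**What to change.** Amend the adherence wording in Statistical methods and in Process evaluation.

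- **High-intensity arm.** Compare the session peak heart rate, already collected, with the above-90% bout target, and report the proportion of sessions that reach it. Where monitor traces are retained, also report the proportion of repetitions above 90%, and state how heart rate within a bout is summarised.
- **Low-intensity arm.** Keep average heart rate against the 40% to 50% band, taken over the activity period and excluding warm-up and cool-down where the data allow.
- **Both exercise arms.** State the averaging window, and report average heart rate as a descriptive measure of separation between the arms.

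Using session peak costs only a change of wording. Its weakness is that it shows the target was reached at least once, so one good bout out of 4 to 12 would count and adherence may be overstated. Scoring by repetition avoids this but needs the traces to be kept. The article describes manual entry by the exercise professional and does not say whether traces are stored, so this should be settled before data entry begins. The change concerns measurement only and leaves the exercise prescription as it is.

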### Process evaluation

Triangulation of the analysis of the intervention logs, focus groups, and case report forms will be used to describe and examine adherence and delivery of all three arms in order to refine the intervention for the full-scale trial. Intervention logs will be rated against the adherence checklist by members of the study team, to identify implementation fidelity and any potential contamination between arms. The focus groups will be transcribed verbatim and thematically analysed [75] using NVivo software. The findings from the focus groups with REPs and MHSWs will be synthesised with the intervention logs and independent observations of the sessions to explore adherence to training content and importantly to offer explanations for adherence and non-adherence. The findings from the focus groups with the young people will be considered along with the fidelity information from intervention logs and observations and quantitative adherence data (i.e. proportions of sessions attended and average heart rate). This will identify necessary modifications to the intervention for the main trial and to generate hypothetical propositions of the circumstances of successful delivery in the main trial.

We will examine reasons for declining to participate in the study and any demographic patterns amongst decliners to facilitate reach and representativeness of our recruitment strategy in the main trial. With reference to particular groups and local strategies outlined by Active Partnerships, recruitment strategies will be reviewed to aid our interpretation of recruitment figures for hard to reach groups of young people, which will then inform any recommended changes to recruitment strategy in the full-scale trial. This analysis will enable us to identify contextual factors that may affect adoption, delivery, and maintenance of the intervention.

### Economic evaluation

Resources required to provide interventions will be measured in all three groups. Resources measured will include the following: staff time; equipment and consumables; premises hire; and staff training. In addition to these resources, an effective intervention may affect the use of health and social care services, as well as costs borne by young people and families. These will be recorded by means of a modified CSRI. The young person will complete as much of this as they are able, in consultation with the MHSW. This would be supplemented with information from the parent/carer where the young person was unsure of any details. The time frame for the CSRI was the preceding 12 weeks. The design of this modified CSRI will be based on previous literature [73], and the intention is to make the questionnaire as simple as possible.

The main outcome of the economic evaluation will be quality-adjusted life years (QALYs). Two instruments capable of estimating QALYs will the used in the feasibility study; the EQ-5D-5L and CHU-9D, both collected at baseline, 14 weeks, and 26 weeks. It is intended to compare these two instruments. And secondly, by examining correlation with the CDI-2, this will inform a choice between the two in respect of the preferred choice for the full study. The analysis of health economics data will be largely descriptive. We will assess the completeness of these instruments and consider appropriate modifications for the main trial where indicated. Any resources identified by the CSRI will be costed using appropriate local and national cost data. This will enable the identification of key drivers of costs, and this will be used to inform the design of the CSRI in the main study.

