**ASSESSMENTS:**							
***CDI-2***	X		X		X	X	
***Demographic information***	X						
***DAWBA (includes SDQ) CYP completed***	X						
***DAWBA (includes SDQ) Carer completed***	X						
***PAR-Q***	X						
***PANAS***			X		X	X	
***Self-efficacy scale***			X		X	X	
***Social Support Scale***			X		X	X	
***Caregiver burden***			X		X	X	
***Adherence***				X			
***Peak and average HR***				X			
***Ratings of Perceived Exertion***				X			
***Measured physical activity***			X		X	X	
***Y-PAQ***			X		X	X	
***COM-B measures***			X		X	X	
***EQ-5D-5L***			X		X	X	
***CSRI***			X		X	X	
***CHU-9D***			X		X	X	
***Focus groups***							X
**ADVERSE EVENT MONITORING**			X	X	X	X	X

Note: *FU* follow-up, *T0* baseline, *T1* first FU, *T2* second FU, *CDI-2* Clinical Depression Inventory – 2, *DAWBA* Development and Wellbeing Assessment, *SDQ* Strengths and Difficulties Questionnaire, *CYP* Child or Young Person, *PAR-Q* Physical Activity Readiness Questionnaire, *PANAS* Positive and Negative Affect Schedule, *Y-PAQ* Youth Physical Activity Questionnaire, *CSRI* Client Service Receipt Inventory, *CHU-9D* Child Health Utility 9D

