##### Baseline and follow-up

Young people and parents will be followed-up at 14 and 26 weeks. To maximise engagement with the young people in the study, baseline and follow-up data collection is planned as a group session (in trial groups), with the young people completing the outcome measures as online questionnaires either on their smartphones, or on tablets provided by the group facilitator. Individual follow-up via online questionnaire will be available where preferred by the young person. Caregiver burden data will be collected from parents via online survey, either at the group session or at home.

Attendance, adherence, and physical exertion data will be recorded on a paper form at each intervention session by the REP, and then entered into the study database immediately after the session has concluded. Heart rate data during the session will be recorded using chest band monitors and relayed to the REP’s tablet via Bluetooth. It will then be entered manually into the study database by the REP.

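### The CSRI's 12-week recall period does not fit the 14 weeks between baseline and first follow-up, leaving up to two weeks of service use and family costs unrecorded

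*Protocol article*

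**What the plan says.** All references are to the protocol article.

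- **Recall period.** Economic evaluation states "The time frame for the CSRI was the preceding 12 weeks", with no exception for any visit.
- **Visits.** Baseline and follow-up states "Young people and parents will be followed-up at 14 and 26 weeks". Table 3 defines T0 as baseline, T1 as +14 weeks and T2 as +26 weeks. It marks the CSRI at T0, T1 and T2, with no administration between T0 and T1.
- **What the CSRI is for.** Of health and social care use and the costs falling on young people and families, Economic evaluation says "These will be recorded by means of a modified CSRI".
- **What is measured another way.** The same section says "Resources required to provide interventions will be measured in all three groups" and lists staff time, equipment and consumables, premises and training.
- **Effects.** QALYs are the main economic outcome. The EQ-5D-5L and CHU-9D are "both collected at baseline, 14 weeks, and 26 weeks".
- **Use of the data.** "The analysis of health economics data will be largely descriptive". The CSRI results are meant to show the main cost drivers and to shape the CSRI for the main study. Feasibility outcomes lists an estimate of resource use at 26 weeks.

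**The concern.** A form that looks back 12 weeks, completed 14 weeks after the previous one, cannot cover the whole interval. The baseline form does not help, because it looks back from week 0. Service use and family costs in the uncovered time are never asked about. Any follow-up total built from the T1 and T2 forms is then too low whenever there was use in that time, and it covers a shorter period than the utility measures.

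The planned checks would not reveal this. Statistical methods judges the feasibility of collecting resource-use data by the proportion of missing data. A period outside the recall window is never registered as missing, so a fully completed set of CSRI forms would still carry the gap.

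**Working it through.** The article gives no derived figure to reproduce. The check is one of interval coverage.

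**Inputs.** Recall period 12 weeks (Economic evaluation). CSRI at weeks 0, 14 and 26 (Table 3; Baseline and follow-up). Utilities at weeks 0, 14 and 26 (Economic evaluation).

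**Formula.** A CSRI completed at week t covers [t − 12, t].

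**Weeks counted from T0**

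| Visit | Window (weeks) |
|---|---|
| T0 | [0 − 12, 0] = [−12, 0] |
| T1 | [14 − 12, 14] = [2, 14] |
| T2 | [26 − 12, 26] = [14, 26] |

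The T1 and T2 windows meet at week 14. Weeks 0-2 lie in no window.

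- Share of the first interval: 2/14 = 14.3%.
- Share of follow-up: 2/26 = 7.7%.
- If use were constant over time (an assumption made only for scale), the T1 form would capture 12/14 = 85.7% of the first interval, and T1 plus T2 would capture 24/26 = 92.3% of follow-up.

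**Departures from the nominal T1 date.** Two 12-week windows cover at most 24 weeks, so with T2 at week 26 at least two weeks are always uncovered.

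- T1 early by e weeks (e up to 2): its window is [2 − e, 14 − e]. The gap is (2 − e) before it plus e after it, 2 weeks in total.
- T1 late by d weeks: its window is [2 + d, 14 + d] and overlaps the T2 window. The gap grows to 2 + d weeks.
- Reading the 3 and 6 months in the Abstract as weeks 13 and 26: the windows are [1, 13] and [14, 26]. Weeks 0-1 and 13-14 are uncovered, again 2 weeks.

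**Weeks counted from randomisation.** Feasibility outcomes counts its 26 weeks from randomisation, and Table 3 places randomisation before T0. If T0 falls L weeks after randomisation, the T1 window still opens at week 2 on that clock but follow-up opens at week L, so the gap is max(0, 2 − L). The article gives no L, so the values below are assumptions.

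| Assumed L (weeks) | Gap (weeks) | Share of follow-up after T0 |
|---|---|---|
| 0 | 2 | 2/26 = 7.7% |
| 1 | 1 | 1/25 = 4.0% |
| 2 or more | 0 | 0% |

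**After the change proposed below.** The windows become [0, 14] and [14, 26], and the uncovered time falls from 2 weeks to 0.

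**The case against.** The strongest reply has four parts.

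1. **The clock is unsettled.** Allocation concealment mechanism describes staff being told of the allocation so that they can set up the intervention, so some lag between randomisation and baseline is plausible. This stands: the two weeks are the result under the natural reading of Table 3, not a certainty. The gap closes only with a lag of two weeks or more, which the article does not state.
2. **There is no cost-effectiveness estimate here to distort.** The economic analysis is largely descriptive, no formal comparison of groups is planned, and no QALY formula or cost-per-QALY calculation is given. The gap is the same by design in every arm. This stands and limits the consequence.
3. **Revising the form is a stated purpose of the study.** True, but the completeness check cannot show this fault, so the planned review might not find it.
4. **One window at every visit is simple and gives directly comparable totals.** The T1 total could be scaled by 14/12. That is possible, but it assumes that use in the unasked weeks ran at the later rate, which the data could not test.

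A reader might go further and infer three things that the article does not support:

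- *All resource use in the first two weeks is lost.* It is not: delivery resources are measured separately, and adverse events are monitored throughout. Adverse event records do not, however, measure service use or family costs.
- *The uncovered weeks are the first sessions, when referrals or reactions peak.* Table 3 places a 12-week programme somewhere between T0 and T1 without fixing its start at T0, and nothing describes how service use changes over time.
- *The gap will pass into the main trial's cost-effectiveness analysis.* It could, but the article provides for changing the form first.

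**Conclusion.** The recall period and the visit schedule do not fit each other, and both are stated in the article. On the natural reading of Table 3, two weeks of health and social care use and family costs after baseline are not captured: 14.3% of the first interval and 7.7% of follow-up. If the schedule runs from randomisation, the gap is max(0, 2 − L) weeks for an unstated lag L.

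The conclusion assumes that the 12 weeks apply at every visit, as written, and that no other source records these items; the article names none. That the utilities span the full 26 weeks is inferred from their measurement times.

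The effect on this feasibility study is modest. It is still worth correcting, because resource use is a listed feasibility outcome and the CSRI is being piloted for the main trial.

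**What to change.** - Word the T1 CSRI as *since your baseline questionnaire* and the T2 CSRI as *since your last questionnaire*, with the dates pre-filled from the study database. This also removes the gap or overlap caused by early or late visits.
- Keep 12 weeks at baseline, and use weekly rates for any comparison with baseline, since the periods then differ in length.
- State whether weeks 14 and 26 are counted from T0 or from randomisation.

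The cost is a small change of wording with a date brought in from the database, about two weeks' longer recall at T1, and unequal recall periods across visits, which the weekly rates handle.
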